### ***1.5 Power considerations***

Since in Part 1 of the study no hypotheses are tested, power calculations are not really applicable. Nevertheless remarks can be made on the precision of the estimates this part of the study will yield.

A sample of 3.100 toddlers (3.000 of the community sample and 100 of the clinical sample) will allow to estimate the area under the Receiver Operating Characteristic (ROC) curve of about 0.90 with a 95% confidence interval of  $\pm 0.02$  (Hanley et al, 1982). A sub-sample size of 217 toddlers (e.g. a specific ethnic sub-group of 7% of the whole population, assuming equal prevalence of emotional and behavioral problems) will allow to estimate the area under the ROC curve of about 0.90 with a 95% confidence interval of  $\pm 0.08$ .

For evaluating concurrent validity of the BITSEA, correlations between specific BITSEA scores and specific, hypothesized CBCL 1,5-5 scores will be computed. Even in a sub-sample of 500 toddlers we can estimate a correlation of 0.20 (or higher) with a power of 99% ( $\alpha = 0.05$ ; one sided testing). An even smaller sub-sample of 50 toddlers (of a small specific ethnic sub-group for instance) will allow to estimate a correlation of 0.40 with a power of 90% ( $\alpha=0.05$ ; one sided testing).

Based on the entire community sample ( $n=3.000$ ) the p90 of the BITSEA Problem Total Score of 2-year olds can be estimated with a precision of  $\pm 3\%$  for boys and girls separately.

### ***1.6 Inclusion schedule and time schedule of the study***

An Inclusion schedule by month and a time schedule by month of Part 1 of the study are included as Annex to the protocol.

---

|                                                        |
|--------------------------------------------------------|
| PART 2 OF THE STUDY: 'BITSEA AS SCREENING TOOL' |
|--------------------------------------------------------|

Part 2 of the study is intended to answer Research questions 2, 3, and 4 (See paragraph on Objectives). Part 2 will establish the outcomes after a follow-up of 12 months, and the feasibility and costs of the BITSEA screening tool. The BITSEA will be applied by 15 YHC centers in the study, and the results will be compared with the results of 'usual care' in 15 other YHC centers (based on randomization) in the varied Rotterdam Rijnmond region. 'Usual care' implies the application of the KIPPPI-2.

Please refer to the attached Annex with a schematic overview of study populations and design regarding Part 2 of the study. Please also refer to the attached Annex with a systematic review of the literature on the BITSEA, including results of follow-up studies, and the absence of such studies in the Netherlands.

### ***2.1 Design and study population***

The study is designed as a cluster-randomized controlled trial (cRCT), with a baseline and a follow-up measurement after 12 months, and a Control condition (screening using the KIPPPI-2) and an Intervention condition (screening using the BITSEA). The YHC team is the unit of randomization (Campbell et al, 2004). The four collaborating preventive YHC organizations for preschool children in the Rotterdam Rijnmond region will participate with 30 YHC-teams. So, 15 YHC-teams will belong to the Intervention group (BITSEA screening) and 15 YHC-teams will belong to the Control group (KIPPPI-2 screening); based on randomization of the teams.

### ***2.2 Procedure***

Prior to the regularly scheduled, routine visit to the preventive YHC-center at child age 24 months, all parents of a 2-year old will be fully informed and invited to participate with their child in the study; written informed consent will be obtained.

As described in paragraph 1.2 (above) prior to the visit, the parents complete the Youth Health Monitor questionnaire as part of the normal routine at the YHC-centers. In the Control group, as usual, the Youth Health Monitor questionnaire includes the KIPPPI-2. In the Intervention group the Youth Health Monitor includes a new questionnaire, i.e. the BITSEA.

As stated above bilingual versions (Dutch; Turkish/Arabic) are available and help can be provided by the YHC-center as part of the regular procedures.

Separately from the Youth Health Monitor, at child age 24 months all participating parents will be invited to complete a concise additional questionnaire anonymously. In the Intervention group this questionnaire contains the CBCL 1,5-5. In the Control group this questionnaire contains the CBCL 1,5-5 and the BITSEA. As stated above, scores from this additional questionnaire at age 24 months will not be used in the routine health assessment (see schematic Overview of the study in Annex).

Trained YHC-professionals (see below for details regarding the training) use either the BITSEA or the KIPPPI-2 as screening tool during the visit. According to the existing protocols, professionals will make use of cut-off points based on the 90th percentile (p90) of age-appropriate normative samples for interpretation of test results, next to other professional

---

observations in the Intervention group (BITSEA; see Briggs-Gowan MJ et al. Brief Infant Toddler Social and Emotional Assessment - BITSEA Manual. New Haven: Yale University; 2005) as well as in the Control group (KIPPPPI-2; see the website of KIPPPPI-2 <http://www.kippipi.nl/>; Jeugdmonitor Rotterdam, 2004).

Twelve months after the 24 months YHC-visit, so at age 36 months, all participating parents in the study will be invited to complete a follow-up questionnaire including BITSEA, CBCL 1,5-5, and items on use of care, items on satisfaction with YHC, and if applicable referral and follow-up care, and satisfaction regarding referral and follow-up.

Furthermore, from the files and registry forms the diagnosis and decisions regarding follow-up care or referral by the YHC-professional at the regular YHC-visit at age 24 months will be retrieved, and at age 36 months, the entries in the child's preventive Youth Health Care record (Electronic Medical File; 'Elektronisch Kinddossier') will be retrieved, as well entries in the child's region-wide registry of Youth Care (providing informed consent by the parents).

#### Numbers in the study:

A total of 6.000 parents/toddlers will be invited. Assuming (at least) informed consent by 50%, 3.000 parents/toddlers will be included. Allowing dropout between baseline and follow-up of 30%, we expect complete data regarding 2.100 parents/toddlers after follow-up.

As stated in paragraph 1.2, all participating YHC-teams and each participating YHC-professional in the study will receive handy, clear, written instructions (fact sheets/charts) about the role of each participant in the study. Instructions will be discussed during regular professional meetings (prior to the start of the inclusion, and also repeatedly during the study). The competences that are necessary to use the BITSEA as a screening tool will be trained in the Intervention group. All YHC-professionals in the Intervention group (mostly the specialized YHC-nurses) will be involved in this training. Since the participating YHC practice organizations contemplate implementing the BITSEA regardless of this study, this training will be scheduled in the normally available time for professional training and education in the organization.

As stated in paragraph 1.2, independent of this instruction/training with regard to the study, in a separate, independent proposal, we have presented a plan for activities to promote the readiness for doing research and to promote the willingness to participate in an optimal way in effectiveness studies by YHC-professionals that will cooperate in the study. For that separate purpose we applied for a so-called "Praktijkbonus" (additional financial support) that will be used to support these efforts of the four practice organizations that cooperate in the study (please refer to the Annex 'Praktijkbonus' attached to this proposal).

#### Note regarding the KIPPPPI-2:

The KIPPPPI-'Consultatie Bureau Signalerings Instrument 2-jarige' will be applied in the 'usual care' group. It is an alternative screening tool for 2-year olds developed by Dr. P. Kousemakers (see <http://www.kippipi.nl/>), has been applied regularly in YHC until now, but was NOT advised by the Invent-group given lack of (international) evidence for validity and effectiveness (Hermanns et al, 2005; Jeugdmonitor Rotterdam, 2004).

---

### **2.3 Measures**

Note: These measures are only available providing informed consent by the parents

#### **Outcomes**

- CBCL 1,5-5 at baseline and 12-month follow-up (CBCL 1,5-5 scores are considered the primary outcomes)
- BITSEA at baseline and 12-month follow-up
- YHC-professional problem diagnosis and treatment/referral decisions at baseline and during follow-up (Reijneveld et al, 2004; Zeijl et al, 2005)
- Entries in the regional Youth Care Registries (SISA/SJS) at baseline and during follow-up (SJS, 2006)
- Child health-related quality of life (General health perceptions subscale of the ITQOL; Raat et al, 2006)

#### **Co-variables (at baseline and at follow-up)**

- Course of pregnancy, medical and family history from medical file; Socio-demographic and environmental variables (Reijneveld et al, 2004; Zeijl et al, 2005)

#### **Process measures**

- Adherence to the distinct elements of the early detection
- Appreciation/satisfaction regarding the early detection
- Time investment/other costs of the procedure.

### **2.4 Data analysis**

Multilevel analyses will be applied to allow for dependency between the individual measurements within the randomized YHC-teams (Campbell et al, 2004; Twisk, 2006). Multilevel linear regression analyses will be conducted for the continuous outcome variables with group (intervention or control) as independent variable and baseline values and potential confounders as covariates. Multilevel logistic regression will be performed in case of dichotomous outcome variables. Interaction effects by gender and ethnic background will be explored by introducing an interaction term into the regression analyses (Twisk, 2006).

Adherence to and satisfaction with the distinct elements of the early detection procedure by parents and professionals will be described.

Costs and effects will be evaluated for the purpose of a cost-benefit analysis.

### **2.5 Power considerations**

At follow-up, we expect complete data of 2.100 parents/toddlers, equally divided over Intervention/Control group. We take alpha of 0.05 and power of 0.8. We apply a correction factor to account for the cluster design (assuming Intra Class Correlation Coefficient to be 0.10). Within the whole study population (n=2.100 for Intervention and Control group combined), for the CBCL 1.5-5 total problems score the study can detect at follow-up a minimal difference between intervention/control group of 8.0 points (SD=26.5) (Achenbach et al, 2000).

---

Within the sub-group in the study with psychosocial problems at baseline (assumed to be 10% of the population at baseline; so 210 in Intervention and Control group combined), for the CBCL 1.5-5 total problems score, the study can detect at follow-up a minimal difference between intervention/control group of 11.9 points (SD=26.5) (Achenbach et al, 2000).

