  9. The costs of the whole screening procedure (including referral, diagnosis, and treatment) should be acceptable in the whole context of (health) care.
  10. The screening process should be well-organized and should be embedded in a continuous program (i.e. not an ad-hoc procedure).

Part 1 and Part 2 of this study will clearly contribute to the empirical knowledge needed to decide on future implementation of screening for emotional and behavioral problems in 2-year olds by using the BITSEA in preventive Youth Health Care in the Netherlands, given the 10 criteria of Wilson and Jungner.

Adequate test properties of the BITSEA (criterion 5) have been established in the U.S.. This study will contribute to the knowledge needed to decide on the plausibility of the BITSEA screening in the Netherlands by evaluating the test properties of the BITSEA in the context of day-to-day practice of preventive Youth Health Care in the Netherlands.

Hypotheses applied in Part 2 of the study:

We hypothesize that use of the BITSEA as screening tool compared to KIPPPI-2, results in more appropriate and timely care; and that fewer problems indicated by the CBCL 1,5-5 will be present at 1 year follow-up in the BITSEA group (Intervention condition) compared to the KIPPPI-2 group (Control condition).

We also hypothesize the (relative) costs of the use of the BITSEA to be lower than the costs of the KIPPPI-2 as screening tool.

---

|                                        |
|----------------------------------------|
| PART 1 OF THE STUDY: 'TEST PROPERTIES' |
|----------------------------------------|

In the Part 1 of the study test properties, including psychometric characteristics, sensitivity, specificity and predictive value of the BITSEA will be studied (Research question 1).

Please refer to the attached Annex with a schematic overview of study populations and design of Part 1 and Part 2 of the study. Please also refer to the attached Annex with a systematic review of the literature on the BITSEA, including a description of the instrument. (see Proposal zomnw)

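### Section 2.5 leaves sidedness and the design effect unstated; under a conventional two-sided 5% test its detectable differences of 8.0 and 11.9 CBCL points become 9.1 and 13.0

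*Protocol*

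**What the plan says.** Protocol section 2.5 holds the only power statement for the cluster-randomised comparison on the CBCL total problems score. On error rates it says: "We take alpha of 0.05 and power of 0.8". On numbers: "we expect complete data of 2.100 parents/toddlers, equally divided over Intervention/Control group". A correction for clustering is applied, "assuming Intra Class Correlation Coefficient to be 0.10", but its formula is not given. For the whole sample the conclusion is that "the study can detect at follow-up a minimal difference between intervention/control group of 8.0 points (SD=26.5". For the subgroup with problems at baseline, taken as 10% or 210 children, it is a "minimal difference between intervention/control group of 11.9 points (SD=26.5".

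Section 2.1 supplies the number of clusters: "So, 15 YHC-teams will belong to the Intervention group (BITSEA screening) and 15 YHC-teams will belong to the Control group".

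Part 2 says nothing on sidedness. Two other places bear on it. The power text for Part 1 (section 1.5) attaches "one sided testing" to both of its correlation calculations. The hypothesis for Part 2, under Study Design, is directional: "fewer problems indicated by the CBCL 1,5-5 will be present at 1 year follow-up in the BITSEA group".

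**The concern.** A bare alpha of 0.05 is normally read as two-sided, and the same protocol adds a label where it means one-sided. On that reading neither stated difference follows from the inputs given: both are about 1.1 points too small. CBCL scores are the primary outcomes (section 2.3), so a reader would credit the trial with 80% power at differences where a two-sided, unadjusted comparison has clearly less. If the authors did mean a one-sided test, the power claim for the primary outcome rests on a choice that Part 2 never declares.

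**Working it through.** **Inputs.** From section 2.5: 2,100 children with complete data, 1,050 per arm; subgroup 210, 105 per arm; ICC 0.10; SD 26.5; alpha 0.05; power 0.80. From section 2.1: 30 teams. The 30% dropout is already removed (3,000 to 2,100, section 2.2). Equal team sizes are assumed: 2,100/30 = 70 children per team, and 210/30 = 7 in the subgroup.

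**Formulas.**
- Design effect: DE = 1 + (m − 1) × ICC
- Standard error: SE = SD × √(2 × DE / n per arm)
- Detectable difference = (z for alpha + z for power) × SE
- Power at difference d = Φ(d/SE − z for alpha)

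**Design effects and standard errors.**
- Whole sample: DE = 1 + 69 × 0.10 = 7.9; SE = 26.5 × √(2 × 7.9/1,050) = 3.251
- Subgroup: DE = 1 + 6 × 0.10 = 1.6; SE = 26.5 × √(2 × 1.6/105) = 4.626

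**Reproducing the plan's figures: one-sided 0.05** (1.645 + 0.842 = 2.486).
- Standard DE: 2.486 × 3.251 = 8.08 and 2.486 × 4.626 = 11.50. Power is 79.3% at 8.0 and 82.3% at 11.9.
- Cruder DE = 1 + m × ICC, giving 8.0 and 1.7: detectable differences 8.13 and 11.86. Power is 78.8% at 8.0 points and 80.3% at 11.9 points.

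So a one-sided test comes close. With the standard DE the 8.0 is nearly recovered and the 11.9 is somewhat conservative. With the cruder DE the 11.9 is recovered and the 8.0 is slightly too low. Neither formula returns both figures exactly.

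**Two-sided 0.05** (1.960 + 0.842 = 2.802).
- Whole sample: 2.802 × 3.251 = 9.11. Power at 8.0 = Φ(8.0/3.251 − 1.960) = 69.2%.
- Subgroup: 2.802 × 4.626 = 12.96. Power at 11.9 = Φ(11.9/4.626 − 1.960) = 73.0%.

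**Could another two-sided reading give the pair?**
- The cruder DE moves further away: 9.17 and 13.36.
- The enrolled numbers (3,000 and 300) give 8.95 and 11.82. The second is close to 11.9, the first is not close to 8.0, and section 2.5 names 2,100 and 210.
- Solving backwards, 8.0 needs a DE of 6.10 and 11.9 a DE of 1.35. With 30 teams these correspond to ICCs of 0.074 and 0.058. At ICC 0.10 they correspond to about 40 and 47 teams. In neither case do the two figures agree with each other or with the protocol.

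| Reading | Whole sample | Subgroup |
|---|---|---|
| Stated in section 2.5 | 8.0 | 11.9 |
| One-sided, DE = 1 + (m − 1) × ICC | 8.1 | 11.5 |
| One-sided, DE = 1 + m × ICC | 8.1 | 11.9 |
| Two-sided, DE = 1 + (m − 1) × ICC | 9.1 | 13.0 |

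**The case against.** **Sidedness is not in the document.** A reader might infer that 8.0 and 11.9 are flat arithmetic errors that no reading can rescue. The protocol does not support that. Section 2.5 does not say two-sided, the Part 2 hypothesis is directional, and the only explicit sidedness in the protocol, in section 1.5, is one-sided. The labels there can be read as the authors' habit as well as a contrast. The remark under Study Design that screening can do harm is general background and does not declare a test. Under a one-sided 5% test both figures lie within about 2 or 3 power points of 80%. This stands, and it makes the two-sided result conditional. It does not settle the matter, because no one-sided test is declared for Part 2 and neither formula gives both figures.

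**The planned analysis adjusts for baseline.** Section 2.4 puts baseline values into the multilevel model, so 69% and 73% are the power of an unadjusted comparison. A reader might infer that the planned analysis itself is underpowered; the protocol does not show that. Purely as an assumption, a baseline to follow-up correlation of 0.46 would bring the two-sided differences to 8.09 and 11.51. But section 2.5 claims no such gain and gives no correlation. Recovering the stated figures exactly would take two different values, about 0.48 and 0.40. Adjustment may therefore restore power, but it does not explain where 8.0 and 11.9 came from.

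**Small-sample degrees of freedom.** With t quantiles on 28 degrees of freedom the two-sided figures are 9.4 and 13.4. This is a refinement that can be left to the statistical analysis plan, and the point does not depend on it.

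**Conclusion.** The point holds in conditional form. Section 2.5 gives its detectable differences without the two items needed to check them: sidedness and the design-effect formula. If the CBCL comparison is tested two-sided at 0.05, the stated inputs give 9.1 instead of 8.0 and 13.0 instead of 11.9, and unadjusted power at the stated differences is about 69% and 73%. If it is tested one-sided at 0.05, the figures are approximately right, but the test is undeclared and the pair does not come from one formula.

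This rests on equal team sizes, the normal approximation, the stated ICC and SD in both populations, and no credit for baseline adjustment. It shows that the power paragraph needs restating. It does not show that the sample size has to change.

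**What to change.** In section 2.5, state that the CBCL comparison is tested two-sided at 0.05, show the design effects 7.9 (70 per team) and 1.6 (7 per team) with their formula, and replace 8.0 and 11.9 by 9.1 and 13.0.

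Two alternatives are open if the authors intend them:
- **One-sided test:** declare it for Part 2, justify it, and restate the pair from one formula; the standard design effect gives 8.1 and 11.5.
- **Credit for baseline adjustment:** state the assumed baseline to follow-up correlation and recompute both figures with the same value.

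The cost is one rewritten paragraph. With the two-sided restatement the figures become slightly less favourable. No extra children or teams are needed, and allocation and analysis stay as planned.

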## ***2.6 Inclusion schedule and time schedule of the study***

A time schedule by month of Part 2 of the study is included as Annex to the protocol.  
An Inclusion schedule by month of the study is also included as a separate Annex to the protocol.

---

## OVERVIEW OF STUDY POPULATIONS AND DESIGN

Validation of the BITSEA and evaluation of the BITSEA as screening tool in Youth Health Care for preschool children

[name], MD, PhD, [name], MSc

[figure not shown]

# INCLUSION SCHEDULE PER MONTH (21 MONTHS)

Validation of the brief Infant-Toddler Social and Emotional Assessment (BITSEA) and evaluation of the BITSEA as screening tool in Youth Health Care for preschool children

[name], MD,PhD, [name], MSc

|                                                                                                                          | 2009 |    |    |    |    |    |     | 2010 |     |     |     |     |     |     |     |     |     |     |     | 2011 |     |
|--------------------------------------------------------------------------------------------------------------------------|------|----|----|----|----|----|-----|------|-----|-----|-----|-----|-----|-----|-----|-----|-----|-----|-----|------|-----|
|                                                                                                                          | J    | J  | A  | S  | O  | N  | D   | J    | F   | M   | A   | M   | J   | J   | A   | S   | O   | N   | D   | J    | F   |
| Parents visiting preventive Youth Health Care Center with a child aged 24 months                                  |      |    |    |    |    |    |     |      |     |     |     |     |     |     |     |     |     |     |     |      |     |
| Inclusion of community sample (n= net 3000; 1500 intervention condition; 1500 control condition)                  | 5    | 10 | 20 | 40 | 60 | 80 | 100 | 125  | 160 | 200 | 200 | 200 | 200 | 200 | 200 | 200 | 200 | 200 | 200 | 200  | 200 |
| Parents referred to or visiting Youth Care (Jeugdzorg) or Youth Mental Health Care with a child aged 18-30 months |      |    |    |    |    |    |     |      |     |     |     |     |     |     |     |     |     |     |     |      |     |
| Inclusion of clinical sample (n= net 100)                                                                         | 1    | 2  | 3  | 4  | 5  | 5  | 5   | 5    | 5   | 5   | 5   | 5   | 5   | 5   | 5   | 5   | 6   | 6   | 6   | 6    | 6   |

|                                                                                                                                                                                                                                                       |
|-------------------------------------------------------------------------------------------------------------------------------------------------------------------------------------------------------------------------------------------------------|
| 
TIME SCHEDULE
 
Validation of the brief Infant-Toddler Social and Emotional Assessment (BITSEA) and evaluation of the BITSEA as screening tool in Youth Health Care for preschool children
 
[name], MD, PhD, [name], MSc
 |
|-------------------------------------------------------------------------------------------------------------------------------------------------------------------------------------------------------------------------------------------------------|

[name], MD, PhD, [name], MSc

\*) preparing protocol, measures, receiving ethical approval, enrol partners for clinical sample, preparing data-entry, selection participating centers)
